**Figure 1 fig1:**
[figure not shown]
The figure illustrates the participant timeline. TBI, traumatic brain injury; MRI, Magnetic Resonance Imaging. * MRI will be performed at 3 and 12 months. **6 months follow-up will be only done in TBI group.

### Study design

This study will be a prospective, longitudinal observational study. We propose to recruit 100 subjects with TBI and 30 orthopedic trauma controls within the first week after the initial injury, matching them for age range and gender. We will follow these patients with physiological, imaging, and cognitive/functional outcome measures over a year (Figure 1).

#### Study population

Patients aged between 18 and 80 years old, within 1-week post-injury, and admitted to the hospital for moderate to severe TBI and/or mild TBI with neuroimaging abnormalities are eligible for inclusion (see Table 1). Additionally, individuals with orthopedic injury without TBI can participate as a control group if they meet the inclusion criteria outlined in Table 1 and do not meet any of the exclusion criteria.

**Table 1 tab1:** Eligibility criteria.

Inclusion Criteria for TBI Group A documented moderate to severe TBI posttraumatic Amnesia (PTA) > 24 h Loss of consciousness (LOC) >30 min Global cognitive score (GCS) <13, or Intracranial neuroimaging abnormalities (Head CT or MRI) Mild TBI with abnormalities on imaging exam. Ages 18–80 years-old 1 week post injury and admitted to the hospital for TBI. All participants must be fluent in English or Spanish. Inclusion Criteria for non-TBI Orthopedic Control Group: Abbreviated Injury Score of ≤4 (not life threatening) for extremity and/or pelvis injury and/or rib fracture Without evidence of TBI based on history or head CT 1 week post injury and admitted to the hospital for trauma. All participants must be fluent in English or Spanish. Exclusion Criteria for the study Significant polytrauma that would interfere with follow-up and outcome assessment. Major debilitating baseline mental health disorders, major debilitating neurological disease, impairing baseline awareness, cognition, or validity of follow-up and outcome assessment. Significant history of pre-existing conditions that would interfere with follow-up and outcome assessment (e.g., end-stage cancers). Patients on psychiatric hold. Prisoners or patients in custody, pregnancy, low likelihood of follow-up (e.g., participants or family indicating low interest, residence in another state or country, homelessness or lack of reliable contacts). Current participant in an interventional trial (e.g., drug, device, behavioral). Penetrating TBI, spinal cord injury with ASIA score of C or worse and contraindications to MRI.

### Recruitment plan

Participants meeting inclusion criteria will be recruited from Parkland Hospital and Texas Health Presbyterian Hospital Dallas. The research coordinator will identify potential subjects daily from various hospital units using electronic medical records and liaising with on-duty medical staff. After screening against criteria, eligible subjects will be approached for study participation.

### Informed consent

Prior to enrollment, the research team will evaluate participants’ competency for informed consent using the Galveston Orientation and Amnesia Test (GOAT). If the GOAT score is below 75, consent from a Legally Authorized Representative (LAR) will be sought and the research coordinator will obtain written permission from that person. All aspects of the study will be thoroughly discussed with patients and legal representatives, and an informed discussion will be undertaken. A copy of the informed consent will be provided to the patient and/or legal representative. For participants consented by an LAR in the acute phase, we will repeat the GOAT assessment and re-consent them during the 3-month follow-up visit.

#### Withdrawal from participation

The patients or their LAR may withdraw the subject from further participation at any time and for any reason. Consistent with Office for Human Research Protections (OHRP) and Food and Drug Administration (FDA) guidance, participant data collected prior to withdrawal from the study is maintained in the study database, but no additional participant data will be collected from the participant or their medical record after withdrawal from the study.

### Follow-up retention plan

The participant or the LAR will be approached at 3 months (±2 weeks), 6 months (±2 weeks), and 12 months (±1 month) for follow-up assessments (Figure 1). For follow-up, participants will be invited to come on 2 days’ visits. On the first day, the patient will undergo a physical neurological exam, as well as cognitive and functional assessments (Table 2). On the second day, a cerebral vascular assessment will be conducted. The MRI will be performed at the University of Texas Medical Center during the first day visit at 3 and 12 months (Figure 1). If participants are still hospitalized at these time points, the follow-up will take place there.

**Table 2 tab2:** Functional, cognitive and psychological health and quality of life.

Domain	Outcome measures	Time points	Interview type
Screening assessment			
	Speech intelligibility	3 M, 6 M*, 12 M	T, IP
	GOAT	3 M, 6 M*, 12 M	T, IP
Comprehensive assessment battery			
Cognition (primary outcome)	NIHTB cognitive battery	3 M, 6 M*, 12 M	IP
	Hopkins Verbal Learning Test (HVLT)	3 M, 6 M*, 12 M	IP
	Trail Making Test	3 M, 6 M*, 12 M	IP
	Processing Speed Index (WAIS-IV PSI)	3 M, 6 M*, 12 M	IP
	SWAPS (aka TAPS)	3 M, 6 M*, 12 M	IP
Global outcomes (secondary outcome measures)	Functional Status Examination (FSE)	3 M, 6 M*, 12 M	T, IP
	Revised Glasgow Outcome Scale Extended (R-GOSE)	3 M, 6 M*, 12 M	T, IP
	Expanded Disability Rating Scale Post-Acute Interview (E-DRS-P)	3 M, 6 M*, 12 M	T, IP
Psychological health and quality of life (secondary outcome measures)	PROMIS PROPr Short form (PROMIS-29 profile V2.1)	3 M, 6 M*, 12 M	T, IP, R
	Pittsburgh Sleep Quality Index (PSQI)	3 M, 6 M*, 12 M	T, IP, R
	NINDS Epilepsy Screening Questionnaire	3 M, 6 M*, 12 M	T, IP
	Rivermead Post-Concussion Questionnaire (RPQ)	3 M, 6 M*, 12 M	T, IP, R
	Patient health Questionnaire-9 (PHQ-9)	3 M, 6 M*, 12 M	T, IP, R
	Columbia Suicide Severity Rating Scale (C-SSRS) (only required if >1 on thePHQ-9 #9)	3 M, 6 M*, 12 M	T, IP
Abbreviated assessment battery for participants who are unable to take comprehensive assessment battery			
Consciousness and basic cognition	Confusion Assessment Protocol (CAP)	3 M, 6 M*, 12 M	IP
	Coma Recovery Scale Revised (CRS-R)	3 M, 6 M*, 12 M	IP
Global outcome	Functional Status Examination (FSE)	3 M, 6 M*, 12 M	T
	Revised Glasgow Outcome Scale Extended (R-GOSE)	3 M, 6 M*, 12 M	T, IP
	Expanded Disability Rating Scale Post-Acute Interview (E-DRS-P)	3 M, 6 M*, 12 M	T, IP

*Only for TBI group; T, telephone interview; IP, in-person interview; O, REDCap online survey.

GOAT, Galveston Orientation and Amnesia Test; NIH ToolBox- Cognitive Battery supplemented; HVLT, Hopkins Verbal Learning Test; WAIS-IV PSI, Processing Speed Index; SWAPS, Southwestern Assessment of Processing Speed; R- GOSE, Glasgow Outcome Scale Extended-Revised; FSE, Functional Status Examination; E-DRS-P Expanded Disability Rating Scale Post-Acute Interview; FIM, Functional Independence Measure; PROMIS PROPr, Patient-Reported Outcomes Measurement Information System; PSQI, Pittsburgh Sleep Quality Index; PTSD, Posttraumatic Stress Disorder; PCL-C, Checklist for Civilians; REDCap, Research Electronic Data Capture.

The participant will be counted as retained in the study when the outcome assessment battery is completed at 12 months post injury. Strategies will be used to maximize retention, such as: (i) during the consent, the research team will make sure that the participant and family fully understand what is involved in the study, (ii) the study coordinator will collect detailed contact information (i.e., primary and backup phone and email) from the family upon consent, and thorough completion of this measure will make future contacts more successful and maximize participant retention, (iii) scheduling follow-up visits at the most convenient time for the participant and using timely visit reminder strategies. Prior to the visit, we will send a confirmation letter including the appointment date, time, location and the duration of the appointment. We will use all available methods to contact the participant (e.g., phone, mail, e-mail, texting, contacting other people listed about how to reach the participant). Every effort will be made to complete the assessment during the visit window.

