### Power and sample size

This study is powered to examine the relationship between the primary outcome of NIHTB_CB fluid composite score at 1-year postinjury and dynamic CA indices derived from frequency-domain analysis during the acute stage of TBI (i.e., <1-week postinjury). According to our previous study (13), the dynamic CA transfer function phase at low frequency range was positively correlated with NIHTB_CB fluid composite score (i.e., a higher phase, a better CA, was associated with better cognitive score), with the coefficient of determination (
$R^{2}$
) of 0.35 (or Pearson correlation coefficient = −0.593). Based on this information, it is estimated that 117 participants (i.e., a cohort of TBI *n* = 90 and orthopedic controls *n* = 27) will provide 82% power at a 5% two-sided significance level to detect a 0.053 increase in 
$R^{2}$
 attributed 2 additional dynamic CA variables (transfer function gain and coherence), adjusting for 6 confounding factors (initial GCS, posttraumatic amnesia, head CT scan, age, sex, and education) in a multiple regression model, where 
$R^{2}=$
0.35 when only the control factors are included in the model (NCSS PASS 16). With a 10% attrition rate, the total sample size of *n* = 130 participants (TBI = 100, control = 30) are required to be enrolled for this study.

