#### Adverse event (AE) and serious adverse event (SAE) reporting

An Adverse Event is any adverse change from the participant’s baseline condition, including clinical or laboratory abnormalities occurring after study consent. Serious Adverse Events include events that are fatal, life-threatening, significantly disabling, result in hospitalization, prolong hospital stays, or are associated with congenital abnormalities or birth defects. Additionally, any experience considered serious by the investigator, or indicating significant hazard, contraindication, side effect, or precaution related to study participation, will be reported as an SAE. The participants will be overseen by physicians and research staff responsible for assessing and reporting AEs and SAEs according to established NIH and University of Texas Southwestern Institutional Review Board (IRB) guidelines. All subjects reporting AE and SAE will be evaluated and treated by physicians as needed. All AE and SAE will be reported to the IRB, NIH, and FDA (when required) to ensure participant safety.

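### Table 2 requires the C-SSRS only above 1 on PHQ-9 item 9; if the item is coded 0 to 3 (assumption), the lowest positive answer does not require it

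*Protocol article*

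**What the plan says.** The rule stands in Table 2 (section Follow-up retention plan), among the psychological health and quality-of-life measures: "Columbia Suicide Severity Rating Scale (C-SSRS) (only required if >1 on thePHQ-9 #9". The instrument that supplies the trigger is the row above it, "Patient health Questionnaire-9 (PHQ-9". Both are scheduled at 3, 6 and 12 months, with the 6-month visit for the TBI group only.

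The two rows differ in how they may be given. The PHQ-9 has interview types T, IP and R; the C-SSRS has T and IP. The legend reads "T, telephone interview; IP, in-person interview; O, REDCap online survey", so R is not defined, and O is defined but not used in the table as printed.

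A separate set of measures is headed "Abbreviated assessment battery for participants who are unable to take comprehensive assessment battery"; it lists neither the PHQ-9 nor the C-SSRS. The article gives no response coding for the PHQ-9 and no other trigger for the C-SSRS. The adverse event section provides general oversight: "The participants will be overseen by physicians and research staff responsible for assessing and reporting AEs and SAEs".

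**The concern.** The trigger is printed as a bare number, and its meaning depends on a coding that the article does not give. Under one plausible coding, a participant who gives the mildest positive answer to the suicidality item is not required to have the structured assessment. Under another, every positive answer already leads to it. Staff who follow the cell literally could therefore apply two different rules.

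What is at stake is participant safety: the cell decides who must have the C-SSRS. The point would weigh more if R stands for the online survey that the legend calls O, which is an assumption. Item 9 could then be answered with no staff member present, and the printed cut-off would be the only prompt in Table 2 for a C-SSRS contact. If R means something else, that extra weight falls away.

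**Working it through.** The plan gives no figure that can be reproduced here. The check is to list the answer levels and count which ones each rule triggers.

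**Inputs**
- Rule as printed: C-SSRS required if item 9 is above 1 (Table 2).
- Coding of item 9: not in the document. Two codings are assumed to show the range, each with one none level and three positive levels: 0 to 3 (0 = none) and 1 to 4 (1 = none).
- Planned enrolment: 100 TBI and 30 controls, with 10% attrition (Power and sample size).
- PHQ-9 visits: 3 per TBI participant and 2 per control, because the 6-month visit is for the TBI group only (Table 2 and its legend).

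**Step 1. Levels that require the C-SSRS**

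| Rule | Coding | Positive levels triggered | None level triggered |
|---|---|---|---|
| >1 (as printed) | 0 to 3 | 2 of 3 (scores 2, 3) | no |
| >1 (as printed) | 1 to 4 | 3 of 3 (scores 2, 3, 4) | no |
| ≥1 | 0 to 3 | 3 of 3 | no |
| ≥1 | 1 to 4 | 3 of 3 | yes |
| any positive response | 0 to 3 | 3 of 3 | no |
| any positive response | 1 to 4 | 3 of 3 | no |

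The printed rule leaves a gap only under 0-to-3 coding, at a score of 1. Changing the sign to ≥1 closes that gap, but under 1-to-4 coding it would send every respondent to the C-SSRS. Only the verbal rule covers all positive answers and spares the none answer under both codings.

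**Step 2. Upper limits on the number affected**
- Participants: 100 + 30 = 130. If the 10% is all lost before 3 months: 90 + 27 = 117.
- PHQ-9 administrations: 100 × 3 + 30 × 2 = 360. With the same early loss: 90 × 3 + 27 × 2 = 270 + 54 = 324.

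These are ceilings under 0-to-3 coding, not estimates. Participants on the abbreviated battery have no PHQ-9 listed, and the document gives no frequency of lowest-level positive answers. Under 1-to-4 coding the number is 0.

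**The case against.** The strongest reply is that nothing here is shown to be wrong. The article states no aim that a cut-off above 1 fails to meet, and a higher cut-off may be deliberate. The coding is outside the document, so the two cases cannot be told apart. Scoring instructions and suicide-risk procedures may well sit in the full protocol or a staff manual, which a journal article need not repeat. The table cell says when an outcome instrument is required and does not claim to be the study's risk-response plan. A neuropsychologist trains and supervises the staff who give the neuropsychological assessment (Functional and cognitive outcomes at 3, 6, and 12 months), and physicians and research staff oversee adverse events.

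Much of this stands. A reader might infer that the study will miss participants with suicidal thoughts. The document does not support that: the gap exists only under an assumed coding, and making the C-SSRS mandatory only above a cut-off sets a minimum, so staff may still give it at a score of 1. A reader might also infer that item 9 will be answered online and unattended. That rests on a second assumption, about the undefined R. That every positive answer should lead to the C-SSRS is this review's recommendation, not a principle stated in the article.

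What does not stand is that the point is merely about missing detail. The article prints a specific numeric trigger, and neither the supervision of staff nor the adverse event section supplies another one in its place.

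**Conclusion.** The point holds as a conditional one. Under 0-to-3 coding (assumption), the printed trigger covers 2 of 3 positive answer levels and does not require the C-SSRS at the lowest. Under 1-to-4 coding it covers 3 of 3 and there is no gap. The number affected lies between 0 and the ceilings worked out above, and the document does not allow it to be narrowed. The rule has no bearing on the primary analysis, power or sample size.

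This is a cheap improvement to a participant-safety rule, not a proven error. It is something the sponsor could change; confidence is low to medium, because the benefit depends on a coding that the article does not give.

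**What to change.** In the C-SSRS row of Table 2, write: *C-SSRS required after any positive response to PHQ-9 item 9 (i.e. ≥1 if coded 0 to 3)*. Make the same change in any staff instruction that repeats the rule.

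The cost is a few words in one table cell. In use, the burden is one additional C-SSRS for each lowest-level positive answer, and Table 2 already allows it by telephone. If the item is coded 1 to 4, the new wording adds no assessments.

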### Data collection

#### Clinical data

In order to standardize data collection and enable comparison, the collection of clinical variables will adhere to a predefined set of National Institutes of Health/National Institute of Neurological Disorders and Stroke Common Data Elements (NIH/NINDS CDEs). These variables encompass a wide range of information including demographics, social status, general health history, injury-related events, physical and neurological examination findings, laboratory test results, vital signs, clinical imaging findings on the initial head computed tomography (CT), hospitalization details, discharge information, and inpatient rehabilitation data. These variables will be collected through chart review and/or patient or family interviews (18, 19).

#### Data sharing plan

The data management and sharing plan will be consistent with the NIH Data Sharing Policy and Implementation Guidance. The Case report form and de-identified imaging data will be made available via the Federal Interagency TBI Research (FITBIR).

#### Physiological data

Cerebral hemodynamic data collection during the acute phase will commence within the first week (as soon as possible after the formal consent) of hospital admission for TBI patients, after which daily monitoring sessions will be performed throughout the first week post injury or until hospital discharge, whichever occurs first (Figure 1). For the OTC group, similar monitoring sessions will be performed as soon as possible after the formal consent.

All measures will be collected under resting conditions and the degree of head-of-bed elevation utilized as the standard of care for each individual will be documented since a patient’s head therapeutic positioning may have effects on cerebral hemodynamics (20).

Non-invasive arterial blood pressure (ABP) will be measured using a finger arterial photoplethysmography device (Finapres Nova, Finapres Medical Systems, The Netherlands), transcranial Doppler ultrasound (Multi-Dop T, DWL, Germany), near-infrared spectroscopy (moorVMS-NIRS, Moor Instruments, United kingdom), electrocardiogram (Finapres Nova, Finapres Medical Systems, The Netherlands), and capnography (Rad-97, Masimo, California, United States) to assess continuous beat-to-beat changes in ABP, cerebral blood flow velocity (CBFV), brain tissue oxygenation, R-R interval, breath-by-breath end-tidal CO_2_ (ETCO_2_) (see Supplementary Figure S1 and Figure 2). Additionally, if available, standard invasive intracranial pressure (ICP) and ABP measurements, as well as ETCO_2_ via mechanical ventilation and other clinically relevant signals, will be collected from the patient’s bedside monitor and integrated simultaneously with the non-invasive physiological signals using ICM+ software (Cambridge Enterprise Ltd., United Kingdom) (21). Monitoring sessions will last for 30 min, with all signals digitized and integrated via an analog-digital converter (DT9826; Data Translation, Marlboro, MA), and recorded using ICM+ software, with a sample rate of 500 Hz.

**Figure 2 fig2:**
[figure not shown]
Intensive Care Unit bedside (ICU) physiological measurement set-up for CAPCOG study: ICU setting (A) cerebral blood velocity waveforms from Dopplerbox (V.10.5.1 software); (B) DWL Dopplerbox; (C) Finometer; (D) Saturimeter; (E) capnograph; (F) Near-Infrared Spectroscopy; (G) dedicated laptop for c data acquisition BIOPAC Systems.

During follow-up, these above mentioned measurements will be repeated (Figure 3), with the addition of electroencephalogram (EEG) (Moberg CNS-300 monitor, Natus, Wisconsin, United States) and 2D color-coded duplex ultrasonography (CX-50, Philips, Massachusetts, United States) to measure volumetric cerebral blood flow (CBF) from the left and right internal carotid artery (ICA) and vertebral artery (VA). Total CBF will be calculated as the sum of blood flow measured from the bilateral ICA and VA. Additionally, cerebrovascular resistance (CVR) will be calculated as mean ABP divided by total CBF.

**Figure 3 fig3:**
[figure not shown]
Follow up setting on the lab. (A) Electroencephalogram (B) Finometer; (C) capnograph; (D) Near-Infrared Spectroscopy; (E) Transcranial Doppler – DWL (F) Eletroencephalogram.

#### Physiological data processing

Cerebrovascular and cardiovascular data will be analyzed using AcqKnowledge (BIOPAC Systems, Goleta, CA), DADiSP (DSP Development Corporation, Newton, MA), MATLAB (MathWorks, Natick, MA) and ICM+ software (22, 23).

Dynamic CA assessed through the different monitoring modalities will be determined in two ways: time domain and frequency domain analyses. Time domain indices are based on the relationship between spontaneous changes in mean arterial pressure (MAP) and CBFV (10, 24–26).

Frequency domain analysis based on MAP-CBFV (TCD-derived), and MAP-Oxyhemoglobin (NIRS-derived) transfer functions will be computed bilaterally in each participant following an international Cerebrovascular Research Network (CARNet) guideline (22). Signals will be sampled (500 Hz) and stored for offline analysis. All signals will be filtered with an eighth-order Butterworth low-pass filter with a cut-off frequency of 20 Hz. The beginning and end of each cardiac cycle will be detected in the BP signal, and mean BP, CBFV and heart rate will be obtained for each heartbeat. Beat-to-beat parameters will be interpolated with a third-order polynomial and resampled at 5 Hz to generate signals with a uniform time base (22). Different TFA parameters (gain, phase, coherence) – will be calculated at very low frequency (VLF, 0.02–0.07 Hz), low frequency (LF, 0.07–0.2 Hz), and high frequency (HF, 0.2–0.5 Hz) ranges (27). Transfer function gain quantifies the magnitude relationship between input and output signals (such as systolic BP and MAP). The phase measures the temporal displacement between the input and output signals, and the coherence measures the strength of the linear relationship between the input and output signals (28).

A final averaged value from the bilateral TCD and NIRS measurements for each index will be calculated to assess *CA.* The CA of affected and unaffected hemisphere side by cranial CT scan will be also analyzed. We propose to use the transfer function phase as the primary measure of CA for its sensitivity and reliability to detect cerebrovascular dysfunction as demonstrated by our team and others (13).

Time domain analysis will be computed utilizing ICM+ software (10). A moving Pearson correlation coefficient calculated between systolic, diastolic, and mean CBFV and MAP using 30 consecutive 10-s windows will be used to derive the TCD-based CA indices systolic flow index (Sx_a) (10), diastolic flow index (Dx_a) (10), mean flow index (Mx_a) and autoregulation index (ARI) (29), respectively. NIRS-based CA indices will be calculated similarly, as the moving correlation between tissue oxygenation index and MAP (TOx_a) and that between tissue hemoglobin index and MAP (THx_a) (30, 31).

